## Abstract

**Background:**

First carpometacarpal (CMC-1) joint osteoarthritis (OA) is a common and disabling condition associated with pain, reduced pinch strength, impaired hand function, and progressive limitations in activities of daily living. Although conservative treatment remains the first therapeutic step, the optimal injectable option for patients with persistent symptoms is still debated.

**Objective:**

To evaluate the clinical efficacy and safety of ultrasound (US)-guided intra-articular injection with low-molecular-weight peptides (LWPs) derived from hydrolyzed collagen in patients with symptomatic CMC-1 OA.

**Methods:**

This protocol describes a prospective single-arm interventional study enrolling patients with symptomatic and radiographically confirmed CMC-1 OA. All eligible participants will undergo US-guided intra-articular injection with LWPs. The primary endpoint will be the change in pain during activity after 3 months. Secondary outcomes will include pain at rest, hand disability, grip and key pinch strength, rescue analgesic consumption, patient-reported improvement, ultrasonographic findings, treatment-related adverse events, and pain during activity and at rest after 1, 3 and 6 months.

**Expected results:**

The study is designed to assess whether the investigational treatment is associated with reduction in pain, improvement in hand function, and an acceptable safety profile over a follow-up period of up to 6 months. A secondary exploratory aim is to identify baseline clinical and US patterns potentially associated with clinical and imaging response.

**Conclusions:**

If supported by the study findings, US-guided intra-articular administration of LWPs may represent a promising minimally invasive therapeutic option for patients with CMC-1 OA who remain symptomatic despite standard conservative care.

## Introduction

Osteoarthritis (OA) of the first carpometacarpal joint (CMC-1), also referred to as thumb-base OA, is among the most common degenerative disorders of the hand and a major source of pain, weakness, and disability in middle-aged and older adults (1–5). Population-based studies show that radiographic CMC-1 OA is common, increases with age, and is more prevalent in women, particularly after menopause (1–3). Occupational and biomechanical exposures involving repetitive pinch, grasp, or thumb loading have also been associated with disease occurrence or progression (4, 5). Clinically, patients typically report pain at the base of the thumb, weakness during pinch and grasp, morning stiffness, crepitus, and progressive limitation in activities such as opening and holding jars, turning keys, handling small objects, or playing a musical instrument (5).

The pathophysiology of CMC-1 OA is multifactorial and includes progressive cartilage degeneration, synovial inflammation, capsuloligamentous laxity, osteophytes formation, and altered joint biomechanics leading to instability and pain (5–7). Imaging studies suggest that thumb-base OA represents a distinct phenotype within hand OA; structural damage, especially osteophytes, may be more strongly associated with pain than inflammatory changes alone (6, 7). Moreover, inflammation plays an important role in this kind of OA when compared to other kinds of OA. In fact, increased synovial and/or capsular vascularization in CMC-1 OA, as a sign of the joint inflammation also contributes to pain severity (7–9). These structural and biological changes contribute to persistent pain, deterioration in hand performance, and reduced quality of life. Standard conservative care is generally stepwise and includes patient education, activity modification, orthoses, pharmacological pain control, and supervised rehabilitation, while intra-articular injection is often considered before surgery when conservative therapy is insufficient (5, 10–13).

Injectable treatments currently used in clinical practice include corticosteroids, hyaluronic acid (HA), and other biological or viscoelastic formulations, but their relative efficacy remains heterogeneous across studies (10–13). In a randomized single-masked study, Monfort et al. reported differential short- and mid-term effects of HA and corticosteroid injections in CMC-1 OA (10), while the RHIZ'ART program by Cormier et al. further explored whether combining HA with corticosteroids improves outcomes compared with corticosteroids alone (11, 12). A recent systematic review and meta-analysis also highlighted the persistent uncertainty surrounding the magnitude and durability of benefit from corticosteroid injections in CMC-1 OA (13). In parallel, interest in collagen-based injectable medical compounds has grown. Reviews of intra-articular collagen therapies and broader collagen derivatives in OA suggest potential symptomatic and structure-supporting effects, although the evidence base remains heterogeneous and still limited (14, 15). Preclinical and clinical studies in knee OA indicate that injectable hydrolyzed collagen may modulate the intra-articular environment, support extracellular matrix homeostasis, and improve pain and function (16–19). According to in-vitro studies, chondrocytes presented significantly smaller cell density and greater matrix deposition after treatment with hydrolyzed collagen (16). Furthermore, high deposition of type-II collagen and inhibition of type-I collagen deposition were observed (16). In animal models, treatment with hydrolyzed collagen decreased levels of pro-inflammatory cytokines, parameters of oxidative stress, as well as cartilage degradation markers (19).

Although most available evidence derives from knee osteoarthritis, similar biological mechanisms may be relevant in small joints, although joint-specific differences should be considered. Evidence in thumb-base OA remains scarce, but recent data on collagen-based filler injection reported encouraging long-term clinical outcomes (20). Hydrolyzed collagen-derived low-molecular-weight peptides (LWPs) have therefore attracted increasing interest as a potentially safe, biologically active option for local treatment (15, 16, 21, 22). In addition, ultrasound (US)-guided LWPs injection has shown preliminary clinical benefit in another degenerative musculoskeletal condition, namely partial supraspinatus tendon tears (23).

US guidance is particularly relevant for the CMC-1 joint because of its small size and complex anatomy. Real-time imaging may improve needle placement accuracy, reduce the risk of extra-articular injection, and enhance procedural standardization. In addition, US enables characterization of joint inflammatory and structural lesions using validated scoring frameworks relevant for hand OA (6, 7, 24, 25). On this basis, the present manuscript proposes a clinical study designed to investigate the efficacy and safety of US-guided intra-articular injection with LWPs in patients with symptomatic CMC-1 OA.

## Rationale and hypothesis

The scientific rationale for this study is grounded in the hypothesis that LWPs may induce a beneficial local effect within the OA joint by supporting matrix turnover, improving the biological milieu, and contributing to symptom control. Experimental and translational studies on collagen derivatives suggest effects on extracellular matrix remodeling, chondrocyte behavior, and inflammatory pathways, while early clinical studies support good tolerability and potential symptomatic benefit after local or intra-articular administration (15–23). Because CMC-1 OA frequently affects fine motor performance and daily functioning, even modest improvements in pain and pinch-related function may have clinically meaningful consequences.

The primary hypothesis is that US-guided intra-articular injection with LWPs will result in clinically meaningful improvements in both resting and activity-related thumb pain at 3 months, while maintaining good local and systemic tolerability.

As secondary outcomes, improvements at 1, 3, and 6 months after the injection are expected in terms of disability assessed with patient-reported measures, grip and key pinch strength, US findings, and a reduction in analgesic use, in the absence of significant adverse events in the weeks following the procedure.

In third instance, this study will seek to identify potential clinical and imaging biomarkers that could predict better outcomes with LWPs injections.

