## Methods

### Study design

This research is conceived as a multicentric prospective single-arm interventional study. Participants with symptomatic and radiographically confirmed CMC-1 OA will receive US-guided intra-articular injection with LWPs. The follow-up period will extend to 6 months; further extensions will be additionally discussed.

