## Eligibility criteria

Eligibility will be established on the basis of clinical, radiographic, and procedural criteria. Table 1 summarizes the proposed inclusion and exclusion criteria.

**Table 1 T1:** Proposed eligibility criteria for enrollment.

Inclusion criteria	Exclusion criteria
Age ≥40 years	Prior thumb base surgery on the affected side
Symptomatic CMC-1 joint OA for over 3 months (joint pain, joint stiffness, decreased mobility, deformity, instability, functional impairment)	Intra-articular injection in the target joint within the previous 3 months
Radiographic confirmation of CMC-1 joint OA using the Eaton-Littler classification	The Eaton-Littler classification grade IV
Pain at the thumb base for at least 3 months	Inflammatory arthritis or crystal arthropathies with treatment changes during the previous 3 months or planned treatment changes during follow-up
Insufficient response to standard conservative treatment	Active local or systemic infection
Average pain intensity ≥4/10 during hand use in the week before enrollment as assessed by NRS for pain	Known hypersensitivity to collagen-derived products or study excipients
Ability to provide written informed consent	Coagulation disorder or anticoagulation judged_incompatible with the procedure
	Pregnancy or breastfeeding
	Neurological or musculoskeletal conditions that could interfere with outcome assessment: carpal tunnel syndrome, ulnar neuropathy, cervical radiculopathy, peripheral neuropathy, multiple sclerosis, stroke, motor neuron disease and Parkinson disease, ligament injuries (e.g., Skier's Thumb) and Dupuytren disease
	History of severe hand and thumb trauma
	Impossibility of safe US-guided injection as assessed by the investigator
	US visible extravasation of the injectate LWPs outside the joint space during the procedure

CMC-1, first carpometacarpal joint; OA, osteoarthritis; NRS, numerical rating scale; US, ultrasound.

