## Intervention

Since this is a multicenter study, to maximize reproducibility, the protocol will provide a detailed description of patient positioning, skin antisepsis, US transducer orientation, needle caliber, approach to the joint, injected volume, and post-procedural recommendations. Moreover, an US calibration exercise will be performed by the sonographers of each center involved in the study. The exercise will be based on a shared database of representative US images. Each sonographer will be asked to score US images in terms of inflammatory and structural findings using semiquantitative scales (0–3) according to the OMERACT hand OA US definitions and semiquantitative scoring system, thereby improving inter-reader standardization before recruitment (24, 25).

Before enrollment, participants will complete visual analog scale (VAS) for pain at rest and during activity, and the Duruöz Hand Index (DHI) and Quick Disabilities of the Arm, Shoulder and Hand (QuickDASH). Grip strength and key pinch strength will be measured with calibrated dynamometer and pinch gauge. To improve comparability across visits and centers, the same device model should be used within each center throughout follow-up and the device characteristics should be recorded a priori.

Baseline US assessment will include the detection and semiquantitative scoring of synovial hypertrophy/effusion, power Doppler signal, and osteophytes, assessed with a high-resolution probe (B-mode frequency >15 MHz; pulse repetition frequency <1.0 kHz) using previously described and validated scanning protocols for hand OA (25).

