## Outcome measures

The primary efficacy endpoint will be the change in pain intensity during activity, measured on a 0–10 NRS (numerical rating scale), from baseline to 3 months. A reduction of 2 points on a 10-point numerical scale is considered a clinically significant improvement in the musculoskeletal setting. Secondary endpoints will include pain at rest, DHI and QuickDASH scores, grip and key pinch strength, rescue medication use, patient global assessment, ultrasonographic findings, and adverse events. This choice is consistent with hand OA trial recommendations, which emphasize pain, physical function, patient global assessment, and—for longer studies—imaging outcomes (27, 28). Table 2 provides a summary of the assessment schedule.

**Table 2 T2:** Proposed schedule of interventions and follow-up assessments.

Assessment	Baseline	1 Month	3 Months	6 Months
Eligibility and consent	X			
NRS for pain at rest and during activity	X	X	X	X
DHI and QuickDASH	X	X	X	X
Grip and key pinch strength	X	X	X	X
US assessment	X		X	X
Injection procedure	X			
Rescue medication review		X	X	X
Adverse events		X	X	X
Patient global assessment/satisfaction		X	X	X

NRS, numerical rating scale; DHI, Duruoz Hand Index; QuickDASH, shortened Disability of Arm, Shoulder and Hand Questionnaire; US, ultrasound.

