## Concomitant treatment

Stable non-pharmacological treatment, including orthoses and prescribed hand exercises, may be continued provided that these measures are documented and remain substantially unchanged during the main assessment phase. Rescue analgesia with acetaminophen/paracetamol and/or non-steroidal anti-inflammatory drugs may be allowed and recorded in patient diaries. Moreover, to minimize confounding effects, concomitant treatments will be kept stable throughout the study period whenever possible and any changes will be carefully recorded and considered in the analysis. The use of additional injections or surgical procedures targeting the study joint during follow-up should be treated as treatment failure or major protocol deviation.

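### The protocol expects analgesic use to fall after the injection, but its schedule takes no pre-injection reading of analgesic use to measure the fall from

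*Protocol article*

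**What the plan says.** In the protocol article, Rationale and hypothesis names four secondary domains in which improvement is expected at 1, 3 and 6 months: patient-reported disability, grip and pinch strength, ultrasound findings, and analgesic use. The last is worded as a fall: "and a reduction in analgesic use, in the absence of significant adverse events in the weeks following the procedure".

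The outcome lists use different terms. The Methods paragraph of the abstract has "rescue analgesic consumption, patient-reported improvement, ultrasonographic findings, treatment-related adverse events", and Outcome measures has "rescue medication use, patient global assessment, ultrasonographic findings, and adverse events". Neither defines the medication outcome as a change from baseline.

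In Table 2 the row "Rescue medication review" is marked at 1, 3 and 6 months and is blank at baseline. The rows for pain, disability and strength are marked at all four time points. The ultrasound row is marked at baseline, 3 and 6 months.

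The pre-enrolment measures under Intervention begin "Before enrollment, participants will complete visual analog scale (VAS) for pain at rest and during activity" and continue with the two disability questionnaires, grip and pinch strength, and ultrasound scoring. Analgesic use is not among them.

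Under Concomitant treatment, rescue paracetamol and NSAIDs "may be allowed and recorded in patient diaries". No diary period before the injection is stated. The same section asks for concomitant treatment to be kept stable where possible and for changes to be recorded.

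Under Study design: "This research is conceived as a multicentric prospective single-arm interventional study".

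**The concern.** A reduction is a statement about two levels, before and after. The printed schedule collects only the second. In a randomised trial, a comparison of post-treatment use between arms could partly make up for a missing baseline; with one arm there is nothing else to compare against.

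Two things are at stake. First, one of the four secondary domains that the protocol sets out would have no result in the form in which it is stated. Second, rescue paracetamol and NSAIDs are permitted, so a reader of the 3-month pain change will want to know whether patients were taking less, the same or more analgesia than before the injection. In an uncontrolled, unblinded study that is useful context, and the schedule does not provide it in measured form.

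**Working it through.** The protocol gives no figure to reproduce here, so the check sets the expectation beside the schedule.

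**Step 1: count the expected changes.** From Rationale and hypothesis: 4 domains × 3 visits = 12 expected changes.

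**Step 2: count those with both readings in Table 2.** A change at a visit can be computed only if the row is marked at baseline and at that visit.

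| Domain | Baseline | 1 month | 3 months | 6 months | Changes computable |
|---|---|---|---|---|---|
| Disability questionnaires | X | X | X | X | 3 of 3 |
| Grip and pinch strength | X | X | X | X | 3 of 3 |
| Ultrasound | X | – | X | X | 2 of 3 |
| Analgesic use (medication review) | – | X | X | X | 0 of 3 |

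Total: 3 + 3 + 2 + 0 = 8 of 12 (67%). Of the four shortfalls, three belong to analgesic use. The fourth, ultrasound at 1 month, is a separate matter and not part of this point.

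**Step 3: look for a reference elsewhere.**

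- Intervention: no analgesic item among the pre-enrolment measures.
- Concomitant treatment: diaries are used, but no run-in or other pre-injection diary period is given.
- Eligibility criteria, Table 1: "Insufficient response to standard conservative treatment" is required. This means that prior treatment is reviewed, but it does not quantify analgesic use at entry.
- Study design: one arm, so no concurrent reference.

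Scheduled readings of analgesic use are therefore 0 before the injection and 3 after it. At 1 month there is no earlier scheduled reading at all. At 3 and 6 months the only earlier readings also follow the injection.

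**Step 4: what the missing baseline means for interpretation.** The values here are assumed for illustration; the document gives none. Suppose a patient reports 4 days of use in the 4 weeks before the month-3 visit.

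- Entry use 8 days: (8 − 4)/8 = 50% reduction.
- Entry use 4 days: (4 − 4)/4 = no change.
- Entry use 2 days: (4 − 2)/2 = 100% rise.

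The scheduled data are identical in all three cases.

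**The case against.** The strongest reply has four parts.

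*Table 2 is not a complete list of baseline data.* It has no row for radiographs or demographics, yet both are needed. A blank cell is therefore weak evidence that nothing is collected, and a medication history could well sit on the case report form. This is fair as to the table alone. But the medication row is present, it is filled in for the three follow-up visits, and the narrative list of baseline measures also omits the item.

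*Entry treatment must be known in some form.* Eligibility depends on response to conservative care, which the Introduction describes as including drug treatment for pain, and changes in concomitant treatment can be recorded only against a known start. This stands as far as it goes. It does not give an amount, and nothing says that use at entry is measured in the same unit and over the same window as at follow-up. As-needed analgesia is the kind of use that a medication list does not quantify.

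*Rescue medication is post-treatment by nature, so an empty baseline cell is normal.* This is right for the outcome as named in the abstract and under Outcome measures, which can be described without a baseline. It leaves the wording under Rationale and hypothesis unsupported. Either the baseline reading is missing or that wording is wrong.

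*A fall between month 1 and month 6 could still be shown.* It could, but it would be a change among post-injection readings, not a reduction from the level before treatment.

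It is also true that this is one secondary domain in a preliminary study, and that even a measured fall could not be attributed to the injection without a control group. That limits the weight of the point without removing it.

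**Conclusion.** The point holds. Followed as printed, the protocol will show how much rescue medication patients use after the injection but not whether use fell from its pre-injection level; 0 of the 3 expected changes in analgesic use can be computed. A value not collected before the injection cannot be supplied by any later analysis, so this goes beyond detail that a statistical analysis plan could fill in.

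The conclusion rests on the schedule and baseline measures as stated in the article. If the case report form already asks for the amount of analgesic use at entry, in the same way as at follow-up, the remedy is only to say so. The effect is confined to a secondary outcome and to the context for reading the pain result; the primary endpoint can be computed as planned. The correction is worth making because it is cheap and is available only before patients are injected.

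**What to change.** Preferred change:

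- In Table 2, mark baseline in the medication row and rename it, for example, *Analgesic and rescue medication use*.
- Ask the same question over the same look-back window at baseline, 1, 3 and 6 months, for example the number of days of analgesic use in the previous 4 weeks. This avoids comparing a recalled baseline with diary-based follow-up.
- Under Outcome measures, define the outcome as change from that baseline.

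The cost is one table mark, one recall question at a visit that already takes place, and one sentence. No visit or procedure is added. The recalled baseline will carry some recall error.

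Alternative, if only post-injection rescue use is of interest: under Rationale and hypothesis, replace the expected reduction with a description of rescue use after the injection. That costs one phrase, and the study then makes no statement about change in analgesic use.

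Either change should be made before recruitment starts.

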## Methods

### Study design

This research is conceived as a multicentric prospective single-arm interventional study. Participants with symptomatic and radiographically confirmed CMC-1 OA will receive US-guided intra-articular injection with LWPs. The follow-up period will extend to 6 months; further extensions will be additionally discussed.

### Study setting and population

The study will be conducted in specialized outpatient settings dedicated to musculoskeletal care. Adults with persistent symptoms despite standard conservative management will be screened for eligibility. Radiographic assessment will be used to confirm diagnosis and to stage the disease severity.

## Eligibility criteria

Eligibility will be established on the basis of clinical, radiographic, and procedural criteria. Table 1 summarizes the proposed inclusion and exclusion criteria.

**Table 1 T1:** Proposed eligibility criteria for enrollment.

Inclusion criteria	Exclusion criteria
Age ≥40 years	Prior thumb base surgery on the affected side
Symptomatic CMC-1 joint OA for over 3 months (joint pain, joint stiffness, decreased mobility, deformity, instability, functional impairment)	Intra-articular injection in the target joint within the previous 3 months
Radiographic confirmation of CMC-1 joint OA using the Eaton-Littler classification	The Eaton-Littler classification grade IV
Pain at the thumb base for at least 3 months	Inflammatory arthritis or crystal arthropathies with treatment changes during the previous 3 months or planned treatment changes during follow-up
Insufficient response to standard conservative treatment	Active local or systemic infection
Average pain intensity ≥4/10 during hand use in the week before enrollment as assessed by NRS for pain	Known hypersensitivity to collagen-derived products or study excipients
Ability to provide written informed consent	Coagulation disorder or anticoagulation judged_incompatible with the procedure
	Pregnancy or breastfeeding
	Neurological or musculoskeletal conditions that could interfere with outcome assessment: carpal tunnel syndrome, ulnar neuropathy, cervical radiculopathy, peripheral neuropathy, multiple sclerosis, stroke, motor neuron disease and Parkinson disease, ligament injuries (e.g., Skier's Thumb) and Dupuytren disease
	History of severe hand and thumb trauma
	Impossibility of safe US-guided injection as assessed by the investigator
	US visible extravasation of the injectate LWPs outside the joint space during the procedure

CMC-1, first carpometacarpal joint; OA, osteoarthritis; NRS, numerical rating scale; US, ultrasound.

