## US-guided injection procedure

All procedures will be performed by an experienced physician trained in musculoskeletal US-guided interventions. The injection will be performed with hand placed on a solid surface with the palm facing upward. A high-frequency linear transducer will be used to identify the CMC-1 joint and to guide needle placement in real time in-plane approach to ensure more precise injection. A single US-guided intra-articular injection of 1 mL of LWPs will be administered into the CMC-1 joint through a 23-gauge needle. Correct intra-articular delivery will be confirmed using US guidance. This approach is methodologically justified in this joint because thumb CMC injections are technically demanding and have lower landmark-based accuracy than several other common hand injections (26).

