## Statistical analysis

Analyses will be performed according to a predefined statistical analysis plan. Because the protocol is currently single-arm and non-randomized, the primary analytical population should include all enrolled participants who receive the injection and provide at least one post-baseline assessment. A per-protocol analysis may be performed as a sensitivity analysis.

Descriptive statistics will summarize baseline demographic, clinical, radiographic, and ultrasonographic characteristics. The primary endpoint—change in pain during activity from baseline to 3 months—may be analyzed with a paired-samples approach or, preferably, with a mixed-effects repeated-measures model including time as a fixed effect and participant as a random effect. Continuous secondary outcomes may be examined with similar longitudinal models, whereas categorical responder analyses may be reported descriptively or explored with appropriate regression methods if sample size permits. Missing data should be handled according to a prespecified strategy consistent with the amount and mechanism of missingness. If sample size allows, exploratory analyses may be performed to assess whether baseline clinical, radiographic, or US features are associated with clinical response (27).

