## Safety monitoring

Safety surveillance will include systematic recording of local and systemic adverse events throughout the study. Particular attention will be paid to post-injection pain flare, swelling, bruising, local inflammatory reaction, hypersensitivity, infection, neurovascular injury, and clinically meaningful worsening of symptoms. Serious adverse events will be reported according to local institutional and regulatory requirements.

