## Ethics and data management

The study will be conducted in accordance with the Declaration of Helsinki, Good Clinical Practice principles, and applicable national regulations. Written informed consent will be obtained from all patients before any study-specific procedure. Ethics committee or institutional review board approval will be secured before the start of recruitment. Study data will be collected through standardized case report forms and stored in a secure database with controlled access.

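### Extravasation seen during the injection is listed as an enrolment exclusion, so the plan selects patients on an event of the treatment itself

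*Protocol article*

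**What the plan says.** Four parts of the protocol article bear on this point.

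- **Eligibility criteria, Table 1.** The table is titled "Proposed eligibility criteria for enrollment". Its last exclusion is "US visible extravasation of the injectate LWPs outside the joint space during the procedure". The row just above it is a separate criterion: "Impossibility of safe US-guided injection as assessed by the investigator".
- **Ethics and data management.** "Written informed consent will be obtained from all patients before any study-specific procedure".
- **Statistical analysis.** "the primary analytical population should include all enrolled participants who receive the injection and provide at least one post-baseline assessment". Extravasation is not mentioned. The section adds: "A per-protocol analysis may be performed as a sensitivity analysis".
- **Safety monitoring.** "Safety surveillance will include systematic recording of local and systemic adverse events throughout the study". Table 2 schedules the adverse event review at 1, 3 and 6 months.

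The article does not say whether a patient with extravasation is followed, analysed, replaced or reported for safety.

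**The concern.** An eligibility criterion should be decidable before treatment. This one is not: it describes something the injection produces. Applied as written, it sorts exposed patients by the technical success of the procedure and keeps the successes.

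Three features of this study make that matter.

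- **No control arm.** Nothing offsets the selection, so it goes straight into the single-arm change from baseline.
- **Extravasation is part of what is being evaluated.** The stated objective is the efficacy and safety of the ultrasound-guided injection. The article gives avoidance of extra-articular injection as a reason for guidance and describes injection of this joint as technically demanding. Where the product goes is thus a result of the intervention, not a patient characteristic.
- **Safety.** The listed events of interest include flare, swelling and local inflammatory reaction. A patient declared ineligible on the day of injection may never reach the 1-month visit, where the first scheduled adverse event review takes place. No later analysis can recover follow-up that was not collected.

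**Working it through.** The plan states no extravasation rate, no outcome by delivery status and no sample size, so there is no figure of its own to reproduce. The check is one of timing and consistency, followed by a calculation for scale.

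**Step 1: timing.** Consent precedes every study procedure, and extravasation is visible only while product is being delivered. Any patient who meets this criterion has therefore consented and been exposed.

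**Step 2: what the row adds.** Patients who cannot be injected safely are already covered by their own row. The extravasation row adds only patients whose injection has begun.

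**Step 3: fit with the primary population.** A patient with extravasation has received an injection and, if followed, will have a post-baseline assessment. Whether that patient belongs to the primary population then turns on the word *enrolled*:

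- If enrolment precedes the injection, the Statistical analysis section includes the patient and Table 1 excludes the same patient.
- If enrolment is completed only after a clean injection, the two texts agree, but enrolment now depends on how treatment went.

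Either way, the selection after exposure remains.

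**Step 4: scale for efficacy.** Let p be the share of injected patients removed and d the mean improvement of those kept minus that of those removed. The mean over all injected patients is (1 − p) × (mean kept) + p × (mean removed). Hence

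overstatement = (mean kept) − (mean over all injected) = p × d.

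Both p and d are assumptions:

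| p | d = 0 | d = 1 | d = 2 |
|---|---|---|---|
| 5% | 0 | 0.05 | 0.10 |
| 10% | 0 | 0.10 | 0.20 |
| 20% | 0 | 0.20 | 0.40 |

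The only documented benchmark is the 2-point reduction that the Outcome measures section calls clinically significant. The largest cell is 0.40 / 2 = 20% of it.

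**Step 5: scale for safety.** The same mixture applies to event rates. Assume a 10% event rate after correct delivery and p = 10%. If the rate after extravasation is 20%, the rate over all injected patients is 0.9 × 10% + 0.1 × 20% = 11%. If it is 40%, the result is 0.9 × 10% + 0.1 × 40% = 13%. If it is also 10%, nothing changes. These rates too are assumptions.

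**The case against.** **Enrolment may be completed only after a successful procedure.** The article says that eligibility rests partly on procedural criteria, and Table 2 puts eligibility, consent and injection at the same baseline visit. On that reading there is no literal contradiction with the primary population. This stands, and a reader who infers two flatly incompatible statements goes further than the text. It does not remove the problem, because enrolment would then be conditional on the course of treatment.

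**Asking what happens when product reaches the joint is a legitimate question.** The intervention is intra-articular by definition, its delivery is to be confirmed by ultrasound, and the article presents the study as preliminary and limited for causal inference. That is fair, but the per-protocol sensitivity analysis already provides a place for that question without losing exposed patients.

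**Stronger readings that the documents do not support.**

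- *The exclusion demonstrably flatters efficacy and safety.* No outcome by delivery status is given, and the bias is zero if outcomes do not depend on delivery.
- *An unblinded operator chooses whom to drop.* The study is unblinded, but this row names no decision-maker, and the 3-month outcome is unknown at that moment.
- *The study has no all-injected safety set.* The article defines a primary analysis population, not a safety denominator, and refers to an analysis plan that is not shown. The safety section exempts nobody from adverse event recording.
- *The requirement of one post-baseline assessment is part of the same fault.* It is a common definition and a separate matter. How missing outcomes are handled is left to a prespecified strategy.

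**Conclusion.** The concern holds in this form: an event of the procedure is listed as an eligibility criterion, so the plan as written can remove consented and exposed patients from efficacy analysis and safety follow-up, and it does not fit cleanly with the primary population. This follows from timing alone and needs no assumed number.

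The size is unknown. Under the assumptions of 5% to 20% removed and a difference of 0 to 2 points, improvement would be overstated by 0 to 0.40 NRS points. A favourable direction is plausible, since patients whose product left the joint might benefit less or react more locally, but nothing in the documents establishes it. The correction should be made before recruitment, because follow-up that is not collected cannot be restored.

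**What to change.** - Remove extravasation from Table 1.
- Record it for every injection as a procedural outcome or protocol deviation.
- Follow these patients on the full Table 2 schedule, including adverse events.
- State that they stay in the primary population as the Statistical analysis section defines it, and in safety reporting.
- Exclude them only in the per-protocol sensitivity analysis.
- Reconcile the Eligibility criteria, Statistical analysis and Safety monitoring sections accordingly. If the sponsor regards enrolment as occurring at a particular moment, the text should say so, and that moment should not depend on how the injection went.

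How extravasation is handled clinically stays with the sponsor.

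The cost is protocol wording, one field on the case report form, and possibly a slightly less favourable efficacy estimate.
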